### Data to be collected

Data collection will occur after informed written consent is obtained by a site principal investigator or delegated member of their research team. Participants will also be asked to decide whether to they wish to give an optional consent for storage of any outstanding samples to a Licensed Biobank at the end of the study. Table 1 lists all of the data points and data collected through the study.

**Table 1 T1:** IMPROVE study research assessments at different time points

	Prevaccine (baseline)	Vaccine date known	1 week before vaccination	At vaccination	1 week after vaccination	3 weeks after vaccination	12 weeks after vaccination
Assessments							
Demographics	*						
Height and weight	*						
Current medication	*						
Comorbidities	*						
Past SARS-CoV-2 vaccines	*						
Serum immunoglobins	*						
Disease activity	*					*	*
Quality of life	*					*	*
Randomisation to include a check that no monoclonal antibody has been received since baseline visit		*					
Reminders of allocation to continue or withhold BTKi			*	*	*		
Adherence to intervention						*	
Check on any monoclonal antibody (prophylaxis or treatment for COVID-19)		*				*	*
Safety						*	*
Details of vaccination						*	
Provision of aide memoire card to participant	*						
Thank you note sent after visit	*					*	*
Samples							
Blood sample taken for anti-spike RBD antibody	*					*	*
Blood sample taken for T-cell ELISPOT	*					*	
Blood sample taken for blood film	*					*	*
Blood sample taken for neutralisation assay	*					*	
Blood sample taken for LDH measurement	*					*	*
Blood sample taken for full blood count measurement	*					*	*
Blood sample taken to be banked for mechanistic work as per section 11				†	†	(No extra blood volume required from that already being taken)*	(No extra blood volume required from that already being taken)*

*Indicates timepoint assessment completed.

†To be taken from 20 participants only.

BTKi, Bruton tyrosine kinase inhibitor; LDH, lactate dehydrogenase; RBD, receptor binding domain.

### Baseline visit

Data on demographic factors (age, sex, ethnicity, height, weight, usual residence (home or residential care)). CLL history (number of lines of therapy, which BTKi is taken and starting dates of therapies), CLL disease activity; bloods taken to measure full blood count (FBC) (haemoglobin, platelet count, lymphocyte count); blood film (presence of prolymphocytes, smear cells or lymphocytosis) and lactate dehydrogenase (LDH) levels; smoking status; self-reported physician diagnosis of comorbidities: diabetes including diet-controlled diabetes, hypertension, ischaemic heart disease, congestive cardiac failure, asthma, chronic obstructive pulmonary disease, high cholesterol, stroke including transient ischaemic attack; current medications; past SARS-CoV-2 vaccines will be collected by the local research team. QoL will be assessed using EORTC-QLQ-CLL17.^32^ Patient global assessment of disease activity will be assessed on a 0–10 NRS for past week using the question:

‘Over the LAST 7 DAYS, in all the ways that your CLL affects you, how would you rate the way you have felt?’ In addition to answering yes or no on whether they have had a temperature greater than 37.5°C, and/or noticed new or enlarged lymph nodes.

### Three weeks PBV (±4 days)

Information about any COVID-19 positive testing, a participant’s global assessment of disease activity will be collected, the latter using the same questions asked at the baseline visit asking for the last 7 days and also in the 3-week period since their booster. QoL will be assessed using EORTC-QLQ-CLL17. These data will be generally collected using a link to the study’s online REDCap database sent in a text message, or by email if participant prefers not to use a mobile phone for this purpose. If a participant prefers not to receive this survey link by email or text, this information will be collected by postal questionnaires or at the study visit.

The local research team will collect data at this visit about a participants COVID-19 vaccination history including the most recent COVID-19 vaccination received, details of any other vaccinations coadministered and adherence to the study intervention. In addition, details of any monoclonal antibody treatment will be collected and bloods taken and blood tests undertaken as at baseline. Details of any SAEs will also be recorded.

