**Methods and analysis:**

An open-label, randomised controlled superiority trial will be conducted in haematology clinics in approximately 10 UK National Health Service (NHS) hospitals. The sample size is 120, randomised 1:1 to intervention and usual care arms. The primary outcome is anti-spike-receptor binding domain (RBD) antibody level at 3 weeks post-SARS-CoV-2 booster vaccination. Secondary outcomes are RBD antibody levels at 12 weeks postbooster vaccination, participant global assessments of disease activity, blood films, full blood count and lactate dehydrogenase levels, impact on quality of life, self-reported adherence with request to temporarily pause or continue BTKi, T cell response against spike protein and relative neutralising antibody titre against SARS-CoV-2 viral variants. Additionally, there will be an investigation of any effects in those given influenza vaccination contemporaneously versus COVID-19 alone.

The primary analysis will be performed on the as randomised groups (‘intention to treat’). The difference between the study arms in anti-spike-RBD antibody level will be estimated using a mixed effects regression model, allowing for repeated measures clustered within participants. The model will be adjusted for randomisation factor (first line or subsequent line of therapy), and prior infection status obtained from prerandomisation antinucleocapsid antibodies as fixed effects.

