We hypothesise that people taking BTKi specifically Ibrutinib or Acalabrutinib for their CLL at the time of vaccination against COVID-19 (±an influenza vaccination) will have an impaired immune response to the vaccine dose, and therefore, lower production of anti-spike-receptor binding domain (RBD) and neutralising antibodies. We propose that a 3-week pause in BTKi treatment will improve the vaccine-specific immune response, without significant worsening of the control of the underlying CLL, when compared with continuation of treatment as usual. The design and delivery of this study was based around another trial that assessed pausing the immune suppressant drug methotrexate around the time of COVID-19 vaccination in patients with inflammatory disorders.^24^ Pausing of CLL therapy is not uncommon and is recommended perioperatively due to the off-target effect of BTKi therapy on platelet function, which results in an increased bleeding risk.^25 26^ Individuals can then experience a disease flare (which can include enlargement of lymph nodes and/or “B symptoms”, such as fever, sweats and weight loss); most are mild with symptoms such as a fever, rash or mild pain, but some can experience raised lymphocyte counts, enlarged spleens, and pain and changes seen in their blood biochemical profiles.

Currently, no randomised trials have examined the impact of pausing BTKi therapy in patients with CLL for vaccine responsiveness. However, several observational studies have shown poorer responses in those taking BTKi and in addition, improvement in responses off therapy. In the CLL-VR study, following the second dose of vaccine, response rates were almost half in patients who took a BTKi compared with healthy controls.^27^ Greenberger *et al* studied responses to a third dose of COVID-19 vaccination in 25 patients with CLL, 13 of whom were treated with BTKi. Of these, 6/13 had an elevated anti-Spike response but 4 had stopped therapy and one was maintained on a low dose. In comparison, among those who continued therapy, five had a very weak response (<5.2 U/mL) and two had an intermediate response (<250 U/mL).^28^ These data suggest that both the proportion of responders and the strength of response increases in patients not taking BTKi therapy.

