#### Experimental arm

To suspend BTKi therapy for 1 week before and 2 weeks immediately after receiving the booster vaccination against COVID-19.

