#### Control arm

To continue the same dose and regimen of BTKi therapy as usual in the week before and weeks after receiving the booster vaccination against COVID-19.

No concomitant care or interventions are prohibited in the study and the participants’ clinical care team will continue to manage their condition in the usual way after the end of their participation in the study.

Automatic reminders by Short Message Service (SMS) or email will be sent to participants to encourage adherence to their randomised intervention, where they consent to receive these. Participants may be telephoned by the study team if they decline the use of SMS or emails for reminders.

Participants and their usual care team will be able to manage any potential tumour flares including with steroids or any other drug as clinically appropriate. Should a clinical need arise, the participants’ usual care team will be able to advise them to continue or not with their allocation. It is known that tumour flare is fully reversible with the reintroduction of BTKi,^25^ and planned dose suspensions are common and do not appear to compromise long-term outcomes such as progression free or overall survival.^31^

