#### Secondary outcomes

Levels of anti-spike RBD antibody at 12 weeks PBV.Participant assessments of disease activity: global assessment using a Numeric Rating Scale (NRS) with 1-week recall at baseline, 3 and 12 weeks PBV, current disease activity level and change since baseline, 3 and 12 weeks PBV.Disease flare-up (tumour flare) and actions taken to deal with them at 3 and 12 weeks PBV.Effect on QoL (assessed using European Organisation for Research and Treatment of Cancer -Quality of Life Questionnaire (EORTC-QLQ-CLL17)) at 3 and 12 weeks PBV.Adherence with advice to pause or continue BTKi: self-report at 3 weeks PBV.COVID-19 neutralising titre at baseline and 3 weeks PBV.T cell responses against ancestral Wuhan and the latest variant of concern (B1, B4, B5 and Sanofi) at baseline and 3 weeks PBV.

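### No stated recall or SAE window covers the first week of the BTKi pause, and the listed 7-day score mainly measures the week after restart, so harm may be understated

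*Protocol article*

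**What the plan says.** The Experimental arm section fixes the intervention: "To suspend BTKi therapy for 1 week before and 2 weeks immediately after receiving the booster vaccination against COVID-19". Table 1 schedules disease activity at baseline, week 3 and week 12 only.

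Under Secondary outcomes, the participant's rating is defined as "global assessment using a Numeric Rating Scale (NRS) with 1-week recall at baseline, 3 and 12 weeks PBV". The same list adds current activity level with change since baseline, and tumour flare with the actions taken. No recall period is given for those two items.

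The baseline questions consist of the numeric rating plus "answering yes or no on whether they have had a temperature greater than 37.5°C, and/or noticed new or enlarged lymph nodes". The section on the three-week visit (±4 days) repeats them "asking for the last 7 days and also in the 3-week period since their booster". The week-12 section describes only the last 7 days.

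Safety outcomes has SAEs recorded from the booster until week 12. The objective on participant-reported disease activity is likewise framed as the 12 weeks after the booster.

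On what happens at restart, the Control arm section states: "It is known that tumour flare is fully reversible with the reintroduction of BTKi". The Introduction hypothesises a better vaccine response "without significant worsening of the control of the underlying CLL", and the Discussion says flare data are collected so that risk can be weighed against benefit.

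**The concern.** The stated windows are anchored to the booster or to the visit, not to the pause. The pause begins a week before the booster and ends a week before the nominal visit. Two things follow.

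- The first week off drug is outside every window whose start is stated.
- The rating named in the outcome list is, at a nominal visit, a rating of the first week back on drug.

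If flare settles once BTKi is reintroduced, as the article says, a score taken after restart would tend to show less difference between arms than existed during the pause. Disease activity is a key secondary outcome and the main evidence on the risk side of the risk/benefit judgement that the trial is meant to inform.

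**Working it through.** The plan gives no figure for this point, so there is none to reproduce. The check is a count of days.

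**Inputs** (booster = day 0)

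- Pause: day -7 to day +14, 21 days (Experimental arm).
- Week-3 visit: day 21, allowed days 17 to 25 (Three weeks PBV).
- Week-3 recall: last 7 days, and booster to visit (same section).
- Week-12 visit: day 84, allowed days 77 to 91; recall last 7 days (Week 12 PBV).
- SAE recording: day 0 to week 12 (Safety outcomes).

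**Formula.** For a window from day a to day b, pause days covered = max(0, min(b, 14) − max(a, −7)).

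**Week-3 windows**

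| Visit day | 7-day window | Pause days in it | Since-booster window | Pause days in it |
|---|---|---|---|---|
| 17 | 10 to 17 | 14 − 10 = 4 | 0 to 17 | 14 |
| 18 | 11 to 18 | 3 | 0 to 18 | 14 |
| 19 | 12 to 19 | 2 | 0 to 19 | 14 |
| 20 | 13 to 20 | 1 | 0 to 20 | 14 |
| 21 | 14 to 21 | 0 | 0 to 21 | 14 |
| 25 | 18 to 25 | 0 | 0 to 25 | 14 |

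- 7-day score: 0/21 pause days at a visit on day 21 or later; at most 4/21 = 19%.
- Since-booster question: 14/21 = 67% at every allowed visit day. The missing 7/21 = 33% is always days -7 to 0.
- Week-12 7-day window: it starts on days 70 to 84, which is 70 − 14 = 56 to 84 − 14 = 70 days after restart; 0 pause days.
- SAE window: 14/21 = 67%, with the same 7 days missing.
- Week-3 blood count, film and lactate dehydrogenase: drawn 17 − 14 = 3 to 25 − 14 = 11 days after restart.
- A recall starting at day -7 would cover 21/21.

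**Consistency of the SAE clock.** The statistical analysis text will report the timing of SAEs from randomisation. Participants are randomised once the booster date is known, and those without time to apply the intervention are excluded, so randomisation comes before the pause. Yet SAEs are recorded only from the booster. An event in the first pause week has a place in the planned summary but no stated route into the data.

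**The case against.** The strongest reply is that the since-booster question is in the same sentence as the 7-day one. It covers two thirds of the pause, including the last two weeks, when time off drug is longest. That stands: only the 7-day score misses most or all of the pause. Early visits (days 17 to 20) also overlap it by 4 to 1 days.

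A reader might infer more than the documents support:

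- **That flare in the first week is never asked about.** The flare item and the change-since-baseline item carry no stated recall period. The full protocol or case report form may fix one that reaches back before the booster. The gap is shown for the numeric rating, the fever and lymph-node questions, and SAEs.
- **That the trial will understate harm.** The article says flare is reversible but gives no time course, and no flare rate. Nothing shows that symptoms or blood values have returned to normal 3 to 11 days after restart. Participants also know their allocation, and expectation could raise reported worsening in the pause arm. Only *may* understate is supported.
- **That a non-significant result will be read as no harm because power is low.** The hypothesis wording sits in the Introduction. Any power figure would need assumed flare rates, and how the flare comparison is interpreted belongs to the separate analysis plan.
- **That the blood measures add to the gap because they are not in the outcome list.** The Abstract names "blood films, full blood count and lactate dehydrogenase levels" as secondary outcomes and the Secondary outcomes list does not. That is a listing inconsistency to tidy, and it has no bearing on recall windows.

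What remains is the set of start dates that the article does state. They are fixed choices in the text, so they cannot be treated as detail left to another document.

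**Conclusion.** The point holds in a limited form. The first 7 of 21 pause days lie outside every explicitly stated patient-reported and SAE window. The 1-week rating in the outcome list covers 0 pause days at a nominal week-3 visit and at most 4. The since-booster question covers 14.

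Given the article's own statement on reversibility, the comparison between arms may understate the harm of pausing. The size cannot be computed, because neither flare rates nor time to resolution are given.

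The count assumes that the pause starts and stops on the planned days, that the questions are answered on the visit day, and that recall windows are applied as worded. The primary antibody analysis is not affected.

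**What to change.** - In both arms, start the retrospective week-3 disease-activity, fever and lymph-node questions 7 days before the booster, or at randomisation. The window must be identical in the two arms so that its length does not itself create a difference.
- Start SAE recording at the same point, which also brings it closer to the planned reporting of timing from randomisation.
- In Secondary outcomes, name that retrospective item as the disease-activity outcome for the pause period. Keep the 7-day rating as a measure of status after restart.
- State the recall period of the flare item.

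The cost is reworded questions, a recall period about a week longer and slightly more SAE recording. No extra visit or blood sample is needed. A short electronic survey at the end of week 2, sent through the existing text or email link, is optional. With a 7-day recall it would cover only about days 7 to 14, so it would supplement the longer retrospective window and could not replace it.

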### Week 12 PBV (±7 days)

Information about any COVID-19 positive testing, any influenza vaccination since the 3-week study visit, the participant’s global assessment of their disease activity will be collected, the latter using the same questions asked at the baseline visit asking about the last 7 days as at week 3. QoL will be assessed using EORTC-QLQ-CLL17 and data will be collected in the methods used at 3 weeks.

The local research team will collect data at this visit about any changes in the participants BTKi prescription, if any NHS services have been sought since the 3-week study visit, or if participants have had any course(s) of steroids since their last visit and details of any monoclonal antibody treatment will be collected. The same bloods and blood tests will be taken as at 3 weeks. Details of any SAEs will also be recorded.

Participants are free to withdraw from the study at any time and all data and samples collected up to the point of withdrawal will be used. Data will be managed and accessible as per the study’s data management plan.

### Sample collection and transport

Blood (10 mL) will be collected in a serum activator tube at baseline, week 3 and 12 visits, along with four lithium heparin tubes (10 mL). These samples will be transported to a central laboratory (the Clinical Immunology Service) at the University of Birmingham by courier. The central laboratory will centrifuge the samples on the day of arrival, aliquot in cryovials and stored at −80°C. They will then be placed into dry ice storage until the analyses are undertaken. For participants recruited at two of the recruiting centres (Birmingham and London), 20 participants will be sought to give optional additional blood samples, specifically the same as collected at the baseline, weeks 3 and 12 visits, within 48 hours and at 1 week PBV.

A further 4 mL EDTA blood tube and 4 mL serum separating blood tube will also be taken at the baseline, 3-week and 12-week visits and processed in the local hospital laboratory to measure FBC and a blood film, and LDH levels accordingly.

#### Laboratory analyses

Anti-spike-RBD (primary endpoint at 3 weeks) and anti-nucleocapsid antibodies: Antibody measurements will be undertaken at the University of Birmingham-Clinical Immunology Service (UoB CIS) using validated commercial assays ROCHE-S and ROCHE-N for anti-spike-RBD and antinucleocapsid antibodies, respectively.^33 34^ROCHE S refers to the Roche Elecsys Anti-SARS-CoV-2 S immunoassay for the in vitro quantitative determination of antibodies (including IgG) to the SARS-CoV-2 spike protein RBD. The assay uses a recombinant protein representing the RBD of the S antigen in a double-antigen sandwich assay format, which favours detection of high affinity antibodies against SARS-CoV-2.ROCHE N refers to the Roche Elecsys Anti-SARS-CoV-2 assay. It uses a modified double-antigen sandwich immunoassay using recombinant nucleocapsid protein (N), which is geared towards the detection of late, mature, high affinity antibodies independent of the subclass. It is a total SARS-CoV-2 antibody assay (IgA, IgM and IgG) detecting predominantly, but not exclusively, IgG.Neutralising antibody titres: Neutralisation assays using pseudotyped virus containing spike protein form Wuhan Hu-1 SARS-CoV-2 and a range of viral variants will be performed at the University of Glasgow on aliquots of the serum collected at baseline and at 3 weeks. All experiments will be conducted in duplicate and absorbance readings will be standardised against positive and negative controls and averaged. Neutralisation curves will be plotted, with the percentage neutralisation modelled as a logistic function of the serum dilution factor (log10). A non-linear regression (curve fit) method will be used to determine the dilution fold that neutralised 50% (IC50) of samples.T cell ELIspot analysis: T cell ELIspot analysis will be performed at the University of Birmingham to detect IFN gamma cytokine release by T cells after extraction of PBMCs from the whole blood received in the lithium heparin tube at baseline and at 3 weeks. All experiments will be conducted in duplicate and absorbance readings will be standardised against positive and negative controls and averaged.Serum immunoglobulins: Serum immunoglobulins will be analysed by the UoB CIS. Quantification of IgG, IgA and IgM will be evaluated using COBAS 6000 (Roche).Anti-influenza antibodies: Serum anti-influenza antibodies will be analysed by the UoB CIS. Specifically, these will be measured by ELISA for 4 H1N1 antigens to reflect the current vaccine component for those that have received a influenza vaccine.

### Data protection and confidentiality

Personal information about potential and enrolled participants will be collected and processed securely, in compliance with the Data Protection Act (DPA) and General Data Protection Regulation (GDPR).

### Sample size and justification

A total of 120 participants will be randomised. The sample size estimates were based on the anti-spike-RBD response after vaccination dose from a small observational study of patients with CLL who were either taking or not taking BTKi.^27^ This suggested a large suppressive effect of BTKi (effect size of 0.9SD). However, anti-spike RBD response related to booster vaccination in CLL patients suggests a smaller though still large effect is more plausible (circa 0.7 SD). Conservatively, we have based the sample size calculation on an effect size of 0.65SD (detecting at least a 0.97 unit (log10 scale) higher antibody response in the BTKi suspension group with 90% statistical power at two-sided 5% significance level which requires data from 102 participants. This leads to 120 participants after allowing for 15% missing data. This calculation was performed using the Stata V.15.1 ‘power twomeans’ command.

Statistical analysis: Full details will be presented in a separate statistical analysis plan which will be drafted and finalised and aimed to be published prior to the final analysis data lock and will receive review and input from the trial steering committee (TSC) and data monitoring committee. The principal analysis will be performed on the as randomised (‘intention-to-treat’) population, analysing participants with available outcome data in their randomised groups, regardless of adherence. The study will be reported in line with Consolidated Standards of Reporting Trials guidelines.^35^

The primary objective of the statistical analysis will be to identify if a temporary 3-week pausing of BTKi around the time of vaccination against SARS-CoV-2 increases the anti-spike-RBD antibody at 3 weeks postvaccine compared with continuing BTKi treatment without interruption. The anti-spike-RBD antibody levels will be summarised descriptively at baseline and 3 and 12 weeks post-COVID-19 booster vaccination follow-up. The differences between the study arms will be estimated using a mixed effects regression model, allowing for repeated measures clustered within participants. The model will be adjusted for a randomisation factor (first line or subsequent line of therapy), and prior infection status obtained from prevaccination antinucleocapsid antibodies, as fixed effects. A treatment by time interaction will be included. The model is anticipated to use an unstructured covariance matrix, and maximum likelihood estimation. Data will be log-transformed prior to analysis, as appropriate. The adjusted mean difference between the groups will be presented, together with 95% CI and p values. The regression model will be simplified (eg, linear regression) if the planned model does not converge.

Supplemental analyses will explore the time effect between the last COVID-19 vaccination dose and the dose given in IMPROVE. The effect of non-compliance to the randomised intervention will be explored using per-protocol analyses.

The same model as for the primary outcome will be used to analyse the 12-week PVB anti-spike-RBD antibody outcome. Similar supportive analyses as planned for the primary outcome will be performed for 12 weeks PVB data. Overall, 50% and 90% neutralisation by Wuhan and VOC along with, T cell spike response by subtype (spike for Wuhan and VOC, and nucleocapsid and membrane), will be analysed in a similar manner to anti-spike RBD antibody outcome. Other secondary outcomes will be analysed using generalised linear models for binary and continuous data, as appropriate, with model adjustment as described above.

The number of SAEs will be presented by treatment arm. The proportion of participants with at least one SAE will be compared. Details of the events will be presented, together with information on the timing of the events from randomisation.

Missing data will be described with reasons given where available; the number and percentage of individuals in the missing category will be presented by treatment arm. No data will be considered spurious in the analysis since all data will be checked and cleaned before analysis.

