### Outcomes

#### Primary outcome

SARS-CoV-2 spike RBD-specific antibody titre at 3 weeks postbooster vaccination (PBV).

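### The stated primary model leaves out the pre-randomisation anti-spike-RBD titre; prespecifying adjustment for it would be a free gain in precision

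*Protocol article*

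**What the plan says.** The primary outcome is the "SARS-CoV-2 spike RBD-specific antibody titre at 3 weeks postbooster vaccination (PBV"). The statistical analysis text, under Sample size and justification, plans a mixed model for repeated measures with an anticipated unstructured covariance. On covariates it says: "The model will be adjusted for a randomisation factor (first line or subsequent line of therapy), and prior infection status", the latter taken from anti-nucleocapsid (anti-N) antibodies. The abstract repeats the set: "The model will be adjusted for randomisation factor (first line or subsequent line of therapy"), again with anti-N status. On time it says: "A treatment by time interaction will be included". If the model does not converge it is to be simplified, with linear regression as the example.

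Table 1 has a row "Blood sample taken for anti-spike RBD antibody", marked at baseline, week 3 and week 12. Randomisation stands in a later column, once the vaccine date is known, so the baseline titre precedes allocation. The Randomisation section stratifies on line of therapy alone. In the analysis text the baseline titre appears only among the descriptive summaries. The article does not say which visits form the outcome vector, and it states no equality of arm means at baseline.

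**The concern.** Participants enter a booster trial with antibody left from earlier doses and infections, so the pre-booster titre on the same assay can be expected to predict the week-3 titre. The Randomisation section accepts this reasoning for past infection, which it calls a strong modifier and brings into the analysis. But anti-N status enters only as prior infection status and cannot carry the titre left by earlier vaccine doses.

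Two things are at stake. One is precision: variation in week-3 titre that baseline would explain stays in the residual. The other is chance imbalance: nothing in the design balances baseline titre, and nothing in the stated model corrects for a difference between arms.

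**Working it through.** **Inputs.** From Sample size and justification: a target of 0.65 SD, expressed on the outcome scale as "detecting at least a 0.97 unit (log10 scale) higher antibody response in the BTKi suspension group"; power 90%, alpha 5% two-sided; 102 evaluable; 15% missing; 120 randomised. Allocation is 1:1, hence 51 per arm. The implied SD is 0.97 / 0.65 = 1.49 log10 units. The correlation *r* between baseline and week-3 log titre, given anti-N status and line of therapy, is not in the article. It is an assumption, shown from 0.3 to 0.8. Below, 1 SD means the residual SD before baseline is used.

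**Step 1: the plan's own figure.** A two-sample t-test with d = 0.65 and two-sided 5% reaches 90% power at 51 per arm (90.2%). So 102 evaluable is reproduced, and 102 / 0.85 = 120. The sample size is correct and assumes no baseline adjustment.

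**Step 2: does the repeated-measures model already use baseline?** Generalised least squares, known covariance, complete data, 51 per arm, week-3 arm contrast:

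- Weeks 3 and 12 as outcomes: SE = √(2/51) = 0.198 SD.
- Baseline, week 3 and week 12 as outcomes, arm means free at every visit: SE = 0.198 SD at every *r*. Both arms have the same saturated time structure, so the contrast is the raw week-3 difference.
- The same three visits, arm means constrained equal at baseline: SE = √(2(1 − r²)/51).

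Only the third gains from baseline in the week-3 contrast. A baseline covariate gives essentially the same SE.

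**Step 3: size of the gain at 51 per arm.** Power uses the t-test with effect 0.65/√(1 − r²). The half-width is 1.96 × SE × 1.49.

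| Assumed r | Residual variance | SE (SD) | Power at 0.65 SD | 95% CI half-width (log10) | Evaluable N an unadjusted analysis would need, 102/(1 − r²) |
|---|---|---|---|---|---|
| none | – | 0.198 | 90% | 0.58 | 102 |
| 0.3 | −9% | 0.189 | 93% | 0.55 | 112 |
| 0.5 | −25% | 0.171 | 96% | 0.50 | 136 |
| 0.7 | −49% | 0.141 | 99.5% | 0.41 | 200 |
| 0.8 | −64% | 0.119 | >99.9% | 0.35 | 283 |

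**Step 4: chance imbalance.** The baseline difference between arms has SD √(2/51) = 0.198 SD. P(|difference| > 0.2 SD) = 2 × [1 − Φ(0.2/0.198)] ≈ 31%; above 0.3 SD it is about 13%. An imbalance reaches week 3 multiplied by *r*, so 0.2 SD shifts the unadjusted difference by 0.2 × 0.3 = 0.06 SD up to 0.2 × 0.8 = 0.16 SD. That is 0.09 to 0.24 log10, against a target of 0.97.

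**The case against.** The strongest reply is that the article does not fix the point. It never says which visits are outcomes, it defers full details to a separate SAP, and a constrained-baseline model would contradict none of its sentences. That is fair, and the SAP may already do this. It does not dispose of the point. The covariate list is stated twice and the same way each time, baseline titre has only a descriptive role, and the fallback regression names no baseline either. A model built from the text as it stands gains nothing from baseline. An effect defined as the difference in change from baseline would use it, but would beat the unadjusted contrast only for *r* above 0.5, and the article does not define the effect that way.

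The second reply is that nothing is invalid. This stands in full: randomisation keeps the estimate unbiased, the confidence interval already allows for chance imbalance, and the promised power holds. It is also true that anti-N status may already capture part of what baseline explains, which is why *r* must be read as a partial correlation and why small values belong in the range.

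A reader might go further and infer four things that the article does not support:

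- **The trial is underpowered or its result biased.** Step 1 and randomisation rule this out.
- **Imbalance passes straight into the estimate.** It is scaled by *r*.
- **The benefit should be judged at an effect well below 0.65 SD.** The calculation targets 0.65 SD, where power is already about 90%.
- **Maximum likelihood estimation inflates the type I error.** That would depend on the reference distribution for the test, which the article does not state.

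**Conclusion.** The point holds as a free improvement, recommended rather than must-fix. The stated primary model omits a pre-randomisation measurement of its own outcome, and a repeated-measures structure with free arm means at baseline does not make up for it. The loss is in precision and in exposure to chance imbalance, not in validity or planned power. The omission and the unchanged SE of 0.198 SD (complete data, 51 per arm) are firm for the model as written. The size of the gain is not: it rests wholly on the assumed *r*, and runs from modest at 0.3 to large at 0.7 and above.

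**What to change.** Before data lock, state in the SAP that the primary model adjusts for baseline log10 anti-spike-RBD titre in one of two ways:

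- as a covariate with a time interaction; or
- by including baseline in the outcome vector with arm means constrained equal at that visit (constrained longitudinal model).

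Keep line of therapy and anti-N status. Carry the adjustment into the fallback regression and the 12-week model, and use the corresponding baseline values in the neutralisation and T-cell models; Table 1 schedules those samples at baseline too.

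The cost is a sentence or two of text, with no new samples, data or participants and no change to the sample size. Timing matters because the Randomisation section says the trial statisticians are not blinded. A covariate added after outcome data have been seen could be taken as a post hoc choice.
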